## Abstract

**Background:**

Almost 60% of transgender people in South Africa are living with HIV. Ending the HIV epidemic will require that transgender people successfully access HIV prevention and treatment. However, transgender people often avoid health services due to facility-based stigma and lack of availability of gender-affirming care. Transgender-specific differentiated service delivery (TG-DSD) may improve engagement and facilitate progress toward HIV elimination. Wits RHI, a renowned South African research institute, established 4 TG-DSD demonstration sites in 2019, with funding from the US Agency for International Development. These sites offer unique opportunities to evaluate the implementation of TG-DSD and test their effectiveness.

**Objective:**

The Jabula Uzibone study seeks to assess the implementation, effectiveness, and cost of TG-DSD for viral suppression and prevention-effective adherence.

**Methods:**

The Jabula Uzibone study collects baseline and 12-month observation checklists at 8 sites and 6 (12.5%) key informant interviews per site at 4 TG-DSD and 4 standard sites (n=48). We seek to enroll ≥600 transgender clients, 50% at TG-DSD and 50% at standard sites: 67% clients with HIV and 33% clients without HIV per site type. Participants complete interviewer-administered surveys quarterly, and blood is drawn at baseline and 12 months for HIV RNA levels among participants with HIV and tenofovir levels among participants on pre-exposure prophylaxis. A subset of 30 participants per site type will complete in-depth interviews at baseline and 12 months: 15 participants will be living with HIV and 15 participants will be HIV negative. Qualitative analyses will explore aspects of implementation; regression models will compare viral suppression and prevention-effective adherence by site type. Structural equation modeling will test for mediation by stigma and gender affirmation. Microcosting approaches will estimate the cost per service user served and per service user successfully treated at TG-DSD sites relative to standard sites, as well as the budget needed for a broader implementation of TG-DSD.

**Results:**

Funded by the US National Institutes of Mental Health in April 2022, the study was approved by the Human Research Ethics Committee at University of Witwatersrand in June 2022 and the Duke University Health System Institutional Review Board in June 2023. Enrollment began in January 2024. As of July 31, 2024, a total of 593 transgender participants have been enrolled: 348 are living with HIV and 245 are HIV negative. We anticipate baseline enrollment will be complete by August 31, 2024, and the final study visit will take place no later than August 2025.

**Conclusions:**

Jabula Uzibone will provide data to inform HIV policies and practices in South Africa and generate the first evidence for implementation of TG-DSD in sub-Saharan Africa. Study findings may inform the use of TG-DSD strategies to increase care engagement and advance global progress toward HIV elimination goals.

**International Registered Report Identifier (IRRID):**

DERR1-10.2196/64373

## Introduction

### HIV Among Transgender People

Transgender people are a key population with a disproportionate burden of HIV. Globally, transgender women have an estimated HIV prevalence of 19.9%, with 66-fold greater odds of HIV compared with other adults, a prevalence that has not decreased over the past decade despite the introduction of HIV pre-exposure prophylaxis (PrEP) [1,2]. Transgender men also face elevated HIV prevalence, with an estimated global prevalence of 2.6% and 6.8-fold increased odds of HIV [2]. South Africa has the largest HIV epidemic in the world, where more than 7 million people are living with HIV [3]. Approximately 17% of the general population of reproductive age adults have HIV, and prevalence is estimated to be 3-fold higher (58%) among transgender people [4]. A recent integrated biobehavioral respondent-driven sampling study (Botshelo Ba Trans [5]; N=888) estimated HIV prevalence in transgender women to be 46% in Buffalo City and Cape Town and 63% in Johannesburg [6-8]. Unfortunately, transgender men and nonbinary people have been largely overlooked in the HIV response, with no available prevalence data from South Africa.

Engaging transgender people in HIV care and prevention is necessary to reach global goals for ending the HIV epidemic by 2030. Global 2020 targets toward ending the HIV epidemic were missed and often left behind key populations, such as transgender people. For example, in 6 of 13 countries reporting HIV data on transgender people to the Joint United Nations Programme on HIV and AIDS (UNAIDS), less than half of transgender women were able to access HIV prevention services [9]. The Global AIDS Strategy 2021-2026 aims to leave no one behind in the HIV response [10]. Therefore, UNAIDS has set more ambitious targets for 95% of people with HIV to be diagnosed, 95% of diagnosed people with HIV to be on antiretroviral therapy (ART), and 95% of people with HIV on ART to achieve sustained viral suppression (ie, 95-95-95) by 2025 [11]. As key populations accounted for 65% of new HIV infections globally and 35% within sub-Saharan Africa in 2020, UNAIDS emphasized the importance of reaching key populations, including transgender people, to achieve these goals [12,13]. Because stigma and discrimination are known drivers of HIV, UNAIDS also set targets for 2025 that include <10% of health workers reporting negative attitudes toward key populations and <10% of key populations reporting experiences of stigma and discrimination [14]. However, interviews with >1400 transgender people in South Africa in 2023 revealed that only 7% felt safe and comfortable when accessing health care; 72% no longer get services because of disrespect from health facility staff; 65% reported that health facility staff were unfriendly; and 10% had been denied health care outright [15].

Although South Africa has the world’s largest HIV epidemic, it has achieved 95% of people with HIV being aware of their status, 77% of people with HIV on ART, and 71% of people with HIV virally suppressed [3]. Unfortunately, South Africa does not disaggregate HIV continuum data for transgender people. In 2019, a study that combined data from transgender women and men who have sex with men in sub-Saharan Africa (including Cape Town and Soweto, South Africa) found that 56% of people with HIV knew their status, 34% were on ART, and 28% were virally suppressed [16]. Another combined study of transgender women and men who have sex with men in Johannesburg found that 47% were virally suppressed. Modeling data from 2021 indicate South Africa will not reach the HIV elimination threshold (incidence <0.1%) without engaging key populations [17]. Modeling has indicated that halving the rate of ART interruptions in South Africa would substantially reduce new infections, accelerating progress toward ending the HIV epidemic [18].

Available data among transgender men [19] and transgender women [20,21] have found suboptimal levels of ART adherence and viral suppression, even in high-income countries. For example, a US-based study of transgender men with HIV found that while 93% had been prescribed ART, only 60% maintained viral suppression over 12 months [19]. Similarly, a US study of transgender women found that while 80% reported ART adherence, only 59% achieved viral suppression [21]. Disaggregated data on viral suppression among transgender people in South Africa are scant. However, an observational cohort study, including 24 transgender women from South Africa, Kenya, and Malawi found that 25% of transgender women were virally suppressed at baseline and 62.5% were suppressed at 12 months [22].

UNAIDS 2025 targets call for 95% of people at risk for HIV acquisition to use combination HIV prevention, including PrEP [11]. However, PrEP uptake is low among transgender women. A large (N=728) US-based longitudinal study of transgender women’s adherence to PrEP during periods of sexual risk (also known as prevention-effective adherence) found it to be <20% [23]. A smaller South African study (N=213) found that less than half of transgender women who were HIV negative reported they had heard of PrEP and only 11% reported taking PrEP [24]. Qualitative interviews with transgender women in the study (n=36) identified health facility-based antitransgender stigma as a barrier to care seeking [24]. While PrEP data on transgender men in sub-Saharan Africa are unavailable, research in high-income countries has found that PrEP-eligible transgender men report low PrEP use (approximately 11%) [25,26], and health care provider stigma is associated with decreased access to HIV prevention services [27]. Our team found no published data on PrEP engagement among gender nonbinary people.

Multiple studies with transgender people have concluded that stigma and limited access to gender affirmation are associated with increased HIV risk and low engagement in HIV care and prevention services [19,20,28,29]. Access to gender-affirming hormone therapy (GAHT) is a priority for many transgender people, often deemed more important than HIV care or prevention [30]. However, a recent study with transgender women in South Africa found that only 17% had access to GAHT [24]. Research has also found that the use of gender-affirming language by health care providers positively impacts transgender patients’ health care experiences, quality of care, mental health, and likelihood of seeking preventive services [31].

### Differentiated Service Delivery

Transgender-specific differentiated service delivery (TG-DSD) is a promising strategy to overcome barriers to HIV service engagement among transgender people. Differentiated service delivery (DSD) is a term used to refer to client-centered approaches that tailor HIV services to reflect the needs of specific populations [32]. Building blocks of DSD include adaptations to when (eg, frequency of clinical visits), where (eg, health facility or community), by whom (eg, nurses or community health workers), and what (eg, ART, PrEP, or counseling) services are offered based on the needs of the individual client [33]. When implemented at scale, DSD is intended to simplify and adapt HIV services across the prevention and treatment continuum in ways that better serve client needs, improve client outcomes, and reduce burdens on the health system [32]. UNAIDS 2025 targets call for 90% of people with HIV and people who face heightened vulnerability to HIV acquisition to be linked to people-centered, context-specific, integrated services, that is, DSD [11].

DSD sites may differentiate services according to client clinical characteristics (eg, newly diagnosed with HIV or stable on ART), subpopulations to which they belong (eg, pediatric, pregnant, or key population), and context in which they live (eg, concentrated versus generalized epidemic and rural versus urban setting) [33]. The World Health Organization (WHO) promotes the use of DSD for key populations to increase service acceptability, quality, and coverage, and reduce costs [34]. Facilities across sub-Saharan Africa have implemented a variety of DSD models for different subpopulations [35-37]. However, South Africa is the first in the region to implement TG-DSD models that tailor services to the specific needs of transgender people, including the need for GAHT.

As GAHT is a priority for transgender people, guidance on DSD for key populations from the WHO [38] and the International AIDS Society [33] recommend the inclusion of GAHT in DSD for transgender people. Promising research in Peru, Thailand, and the United States suggests that integration of GAHT services with HIV care and prevention can improve engagement with HIV services [39-42]. However, the evidence base is limited to case studies or protocols lacking outcome data [39,41,43,44], cross-sectional associations between the use of GAHT and engagement in HIV services [45,46], or outcomes and perceptions of services at a single site [40,42,47]. No published studies compare HIV outcomes at TG-DSD sites versus standard service delivery (SSD) sites, and no published studies of TG-DSD have been conducted in sub-Saharan Africa, the region with the greatest burden of HIV [35].

A recent review of DSD models called for a deeper understanding of their mechanism of effect and noted that while the success of DSD implementation may differ based on a variety of factors, few studies have evaluated comparative implementation or cost [48]. To inform ongoing efforts to achieve UNAIDS goals and leave no one behind, data are needed on the effectiveness of TG-DSD models for improving engagement in HIV services and on implementation barriers, facilitators, acceptability, feasibility, and cost.

Wits RHI demonstration sites provide a unique opportunity to evaluate TG-DSD in sub-Saharan Africa [49]. Over the last several years, Wits RHI has collaborated with transgender-led organizations in 4 municipal areas (Gauteng, Cape Town, Nelson Mandela Bay, and Buffalo City) in South Africa to implement a TG-DSD site in each area (n=4 sites). Each site integrates gender-affirming care, including GAHT, with a full package of facility-based and community-based (mobile) HIV care and prevention services, consistent with the WHO key population and DSD guidelines [49-51]. All staff members receive training on the provision of nonstigmatizing, gender-affirming services. Clinicians receive additional competency training in gender-affirming medical care. These real-world sites, currently supported by programmatic (nonresearch) funds from United States Agency for International Development, provide an important opportunity to conduct much-needed implementation research [32,34,52]. Findings will not only directly inform the future direction of DSD strategies in South Africa but also advance the knowledge base on *if* and *how* TG-DSD models work and the cost of implementation.

A robust evidence base supports DSD among nonkey populations. A systematic scoping review of DSD for HIV treatment included 40 publications (18 from South Africa) involving over 240,000 participants spanning 9 countries in sub-Saharan Africa [35]. The review found that a variety of DSD models were effective for improving viral suppression and retention in care compared with SSD. DSD improved acceptability and, in some cases, reduced the cost of care to clients. While these data provide a strong scientific premise for evaluating DSD models, none of the evaluated DSD models focused on key populations.

### Study Aims and Hypotheses

This study, titled Jabula Uzibone (a Zulu phrase that can be translated into English as “be happy, see yourself”), is designed to fill an important gap in data on implementation, effectiveness, and cost of TG-DSD models in sub-Saharan Africa. It has the aims presented in Textbox 1.

Jabula Uzibone study aims.
**Aims**
Aim 1: assess the barriers, facilitators, acceptability, and feasibility of transgender-specific differentiated service delivery (TG-DSD).Aim 2: evaluate the effect of TG-DSD on viral suppression and prevention-effective adherence and test stigma and gender affirmation as mediators.Hypothesis 1: rates of viral suppression (HIV RNA <50 copies/mL) are more likely to increase among transgender people on antiretroviral therapy (ART) at TG-DSD sites than among transgender people on ART at standard service delivery (SSD) sites over the 12-month study period.Hypothesis 2: rates of prevention-effective adherence (measured by tenofovir levels >700 fmol/punch among participants on pre-exposure prophylaxis [PrEP] or no condomless intercourse among participants who are HIV negative and not taking PrEP) are more likely to increase among participants at TG-DSD sites than among those at SSD sites over the 12-month study period.Hypothesis 3: stigma and gender affirmation will mediate relationships between service delivery models (TG-DSD vs SSD) and HIV outcomes (viral suppression and prevention-effective adherence).Aim 3: estimate the cost associated with TG-DSD versus SSD using a microcosting approach to determine the cost per service user served and per service user successfully treated at TG-DSD sites relative to SSD sites, as well as the budget needed for successful South Africa–wide implementation.

## Methods

### Overall Study Design

Jabula Uzibone is an observational, multisite, mixed methods, and prospective implementation study. To meet the first aim, we will assess the implementation of TG-DSD models and SSD models at the facility level using standardized observation checklists at 8 facilities (1 DSD site and 1 SSD site per area in all 4 areas). We will examine implementation, acceptability, feasibility, and barriers to and facilitators of TG-DSD via key informant interviews (KIIs; n=6 per site) with health facility staff. At the client level, we will conduct in-depth interviews (IDIs) with 30 transgender people (15, 50% from DSD sites and 15, 50% from SSD sites) drawn from the longitudinal cohort enrolled for aim 2 described in the next paragraph.

To meet the second aim, we will enroll a cohort of ≥600 transgender people and follow them for 12 months. Of the transgender people enrolled, ≥400 (66.7%) will be transgender people living with HIV. This will include ≥200 (50%) who receive ART at TG-DSD sites and ≥200 (50%) who receive ART at SSD sites in the same area as the TG-DSD sites. We will also enroll ≥200 transgender people without HIV. This will include ≥100 (50%) participants without HIV at TG-DSD sites and ≥100 (50%) without HIV at SSD sites in the same area as the TG-DSD sites. Each participant will complete a quarterly survey to assess engagement in HIV prevention and care, changes over time in experiences of gender affirmation, and experiences of stigma.

For participants on ART, we will measure HIV RNA levels (ie, viral load) at baseline and 12 months. For participants on PrEP, we will measure tenofovir levels at baseline and 12 months. For participants who are HIV negative and not on PrEP, we will assess self-reported condomless sex. Prevention-effective adherence is defined as being HIV negative and meeting one of the following criteria: (1) adherent to PrEP based on tenofovir levels, (2) self-report of consistent condom use in the prior 30 days, or (3) self-report of no anal or vaginal sex in the prior 30 days. Table 1 presents a list of data collection activities organized by level of analysis, participant type, and month of enrollment.

**Table 1 table1:** Data collection activities by level of analysis, participant type, and month of enrollment.

Level			Participant, n (%)		Baseline		Months 3, 6, and 9		Month 12

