The second hypothesis is that rates of prevention-effective adherence are more likely to increase among transgender people who are HIV negative at TG-DSD sites than among those at SSD sites, over the 12-month study period. We will follow the same steps outlined above for the primary hypothesis. However, we define the outcome measure (prevention-effective adherence) as the proportion of (1) participants on PrEP with TFV levels >700 fmol/punch and (2) participants who are not on PrEP who report no condomless intercourse during the prior 30 days. The estimate will be the absolute difference in the change in the proportion who achieve prevention-effective adherence during the study period comparing those at TG-DSD versus SSD sites. In addition, we will estimate the difference between TG-DSD and SSD sites at 12 months, considering baseline values.

Clients who receive SSD services on enrollment may switch to TG-DSD over time, thereby reducing the sample size of the SSD arm and creating a threat to internal validity. To identify and account for switches over time, we will update information about where the participant is receiving care at every study visit. Participants who transfer from an SSD site to a TG-DSD site will be censored after the date of their last visit for the primary analysis. It would be inappropriate and unethical to require participants to continue receiving care at a specific site, therefore we will use careful tracking to inform an exploratory dose-response analysis that considers the amount of time a participant received care at the TG-DSD sites. The amount of time receiving care at the TG-DSD site will be the independent variable, with the change in outcome from baseline to 12 months as the dependent variable.

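### The Hypothesis 2 outcome is defined two ways, which disagree on PrEP users with low tenofovir who use condoms consistently or report no sex

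*Protocol article*

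**What the plan says.** The outcome is set out in three places.

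- **Overall Study Design:** "Prevention-effective adherence is defined as being HIV negative and meeting one of the following criteria". The first two criteria are "1) adherent to PrEP based on tenofovir levels, (2) self-report of consistent condom use in the prior 30 days". The third is reported abstinence from anal and vaginal sex over the same period. No criterion is tied to PrEP status. The sentence just before this definition reads "For participants who are HIV negative and not on PrEP, we will assess self-reported condomless sex".
- **Textbox 1, Hypothesis 2:** "tenofovir levels >700 fmol/punch among participants on pre-exposure prophylaxis [PrEP] or no condomless intercourse among participants who are HIV negative and not taking PrEP".
- **Data Analysis for Aim 2:** the successes among PrEP users are "1) participants on PrEP with TFV levels >700 fmol/punch". Those among everyone else are "2) participants who are not on PrEP who report no condomless intercourse during the prior 30 days".

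Table 3 lists the survey items for this outcome. The condom item is filtered only on having reported sex in the past 30 days, and the sex item shows no filter. Only the missed-pills item depends on PrEP use.

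The same outcome is a dependent variable in the mediation model (Hypothesis 3). It is also the definition of a successful outcome for HIV-negative clients in the Aim 3 cost analysis. No section says which definition prevails.

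**The concern.** One outcome has two scoring rules, and only one of them can be programmed. Under the rule in the design section, a person succeeds by any of three routes, whatever their PrEP status. Under the split rule in Textbox 1 and the analysis section, being on PrEP closes the behavioural routes.

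The split rule has a consequence of its own. HIV-negative participants are enrolled whether or not they take PrEP, so status can change during the 12 months. Someone protected by condoms or abstinence who starts PrEP and has low tenofovir moves from success to failure with no change in sexual behaviour. Under the any-one-criterion rule this cannot happen. If PrEP uptake changes differently at TG-DSD and SSD sites, the choice of rule therefore moves the Hypothesis 2 estimate, and the mediation and cost-per-success results use the same outcome. If the choice is made after the data are seen, it becomes an analyst's option.

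**Working it through.** **Step 1: where the rules differ.** All nine combinations of PrEP status, tenofovir (users only) and 30-day behaviour, for an HIV-negative participant:

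| PrEP | Tenofovir | Behaviour | Any one criterion | Split rule |
|---|---|---|---|---|
| On | >700 | No sex | Success | Success |
| On | >700 | Always condoms | Success | Success |
| On | >700 | Condomless sex | Success | Success |
| On | ≤700 | No sex | **Success** | **Failure** |
| On | ≤700 | Always condoms | **Success** | **Failure** |
| On | ≤700 | Condomless sex | Failure | Failure |
| Off | – | No sex | Success | Success |
| Off | – | Always condoms | Success | Success |
| Off | – | Condomless sex | Failure | Failure |

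Seven of nine agree. The two that differ are PrEP users at or below threshold who report no sex or consistent condom use.

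**Step 2: gap in one arm at one time.** Let f be the share on PrEP, l the share of users at or below 700, and c the share of those users with no sex or consistent condoms. The any-one-criterion proportion exceeds the split-rule proportion by f × l × c. The documents give none of these, so they are assumed: f 10–70%, l 30–80%, c 20–60%.

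- Lowest: 0.10 × 0.30 × 0.20 = 0.6 points
- Middle: 0.30 × 0.50 × 0.40 = 6.0 points
- Highest: 0.70 × 0.80 × 0.60 = 33.6 points

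**Step 3: effect on the planned estimate.** Hypothesis 2 is estimated as the difference between arms in the change from baseline, so only a differential change in f × l × c matters. Assume f rises from 30% to 50% at TG-DSD sites and stays at 10% at SSD sites, with l and c constant. The differential change in PrEP use is D = (0.50 − 0.30) − (0.10 − 0.10) = 0.20, and the two estimates differ by D × l × c:

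- l = 30%, c = 20%: 0.20 × 0.30 × 0.20 = 1.2 points
- l = 50%, c = 40%: 0.20 × 0.50 × 0.40 = 4.0 points
- l = 80%, c = 60%: 0.20 × 0.80 × 0.60 = 9.6 points

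With the planned 100 HIV-negative participants per site type, the middle case is about four people in the TG-DSD arm.

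**Step 4: direction.** Let a = 1 − l be the share of users above threshold. Assume further that c is the share without condomless sex in every group, on or off PrEP. The success proportion is f·a + (1 − f)·c under the split rule and c + f·a·(1 − c) under any one criterion. Taking the difference-in-difference, a change in uptake alone contributes D × (a − c) and D × a × (1 − c) respectively:

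| a | c | Split rule | Any one criterion | Gap |
|---|---|---|---|---|
| 70% | 20% | 0.20 × 0.50 = +10.0 | 0.20 × 0.70 × 0.80 = +11.2 | 1.2 |
| 50% | 40% | 0.20 × 0.10 = +2.0 | 0.20 × 0.50 × 0.60 = +6.0 | 4.0 |
| 20% | 60% | 0.20 × (−0.40) = −8.0 | 0.20 × 0.20 × 0.40 = +1.6 | 9.6 |

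Under the split rule, rising uptake lowers measured success only when a is below c. Under any one criterion it never does.

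**The case against.** The best defence is that the design section is only a loose summary. The sentence before its definition speaks of condomless sex for people not on PrEP. Strengths and Limitations likewise describes self-report as applying to those not prescribed PrEP. Read that way, the second and third criteria silently apply to non-users, and the analysis section gives the programmer a clear rule. This has some support, but it does not remove the conflict. The one sentence worded as a definition carries no such limit, and Table 3 collects the condom item without a PrEP filter. Even on the charitable reading, the definition needs rewording.

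Other parts of the defence stand:

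- The disagreement touches one narrow group.
- A gap in PrEP use that already exists at baseline largely cancels in a difference-in-difference. Such a gap is plausible, because the TG-DSD sites opened in 2019 and enrolment began in 2024. SSD sites also offer PrEP.
- Neither rule is neutral. The any-one-criterion rule can only gain from PrEP uptake, and it extends self-report to PrEP users although the article names recall and social desirability bias as limitations.

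A reader might infer that the split rule always penalises the arm with more PrEP uptake, or that Hypothesis 2 will change sign with the rule chosen. The documents support neither. The direction depends on whether the share of users above threshold is below or above the share without condomless sex, and the documents report neither share for this cohort.

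**Conclusion.** The contradiction is in the text and affects PrEP users at or below 700 fmol/punch who report no sex or consistent condom use. Under the assumed differential rise in PrEP use of 20 percentage points, the choice of rule moves the Hypothesis 2 difference-in-difference by about 1 to 10 points. It moves it by nothing if the share of such users changes equally in both arms. These figures rest wholly on assumed PrEP use, tenofovir and behaviour shares, held constant apart from PrEP use. The single-time gaps of 0.6 to 33.6 points must not be read as the effect on Hypothesis 2.

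This should be fixed but is not critical. Viral suppression is the primary outcome and the basis of the power calculation. How to count seroconversions is a separate question that this conflict does not settle.

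**What to change.** Before analysis, state one rule in identical terms in Textbox 1, Overall Study Design and Data Analysis for Aim 2, and report the other as a sensitivity analysis. The mediation and cost sections refer to the outcome by name and would follow without rewording.

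The any-one-criterion rule is the better fit to the stated concept. The Introduction ties prevention-effective adherence to periods when there is sexual risk. Strengths and Limitations justifies the broad outcome because behaviour and the indication for PrEP change over time. Scoring a PrEP user who has no sex as a failure sits badly with both. The Introduction's wording does not itself speak to condom use, so that part remains a choice for the investigators to justify.

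The cost is wording and one extra analysis, since the planned tenofovir and Table 3 data allow either rule to be computed. The downside of the preferred rule is more reliance on self-report among PrEP users, which the split-rule sensitivity analysis would show.
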